## Outcomes

### Primary outcomes

Adherence rate: Proportion of patients in the TRE arm adhering to the 16:8 schedule on ≥ 80% of days over the 12-week intervention, reported with a 95% confidence interval (CI).

Therapy response (CR/MRD rate at end of treatment): The combined rate of CR and/or MRD negativity in bone marrow (BM) at end of therapy. CR is defined by IMWG criteria, and MRD negativity at a sensitivity of 10^–5^ by fluorescence-activated cell sorting (FACS) or next-generation sequencing (NGS) on BM aspirate. The fraction will be compared between arms as an exploratory efficacy signal.

### Secondary outcomes

#### Depth of haematologic response

Rates of other IMWG response categories at T_1_, including very good partial response (VGPR), partial response (PR), and stable disease (SD), in each arm. Stringent CR (sCR) will also be noted.

#### Survival outcomes

We will record PFS and OS during and after the trial. PFS is defined from randomisation to disease progression, relapse, or death, and OS from randomisation to death from any cause. Given the study’s design, these data will be descriptive.

#### Patient nutritional status and dietary adequacy

Changes in body weight, BMI, waist circumference, NRS-2002 score, and body composition (phase angle via bioelectrical impedance analysis) will be tracked from baseline through treatment and follow-up. Laboratory markers of nutritional status (albumin) and metabolic biomarkers (glucose, ketones, insulin, and IGF-1) will be measured at baseline and T_1_.

#### Safety and tolerability

The incidence of AEs and serious adverse events (SAEs) will be compared between arms, with attention to ≥ grade 3 according to the NCIC Common Terminology Criteria for Adverse Events (CTCAE) AEs. We will examine if the TRE arm has any increase in events like dehydration, electrolyte imbalances, infections, or other complications.

#### Quality of life (QoL)

Patient-reported outcomes will be measured using the EORTC QLQ-C30 questionnaire at baseline, end of treatment, and end of follow-up.

#### Fatigue

Fatigue will be assessed by the FACIT-fatigue scale (Functional Assessment of Chronic Illness Therapy-Fatigue).

#### Exploratory biological endpoints

The trial will collect biological samples to investigate mechanistic effects of TRE. BM and blood specimens at baseline and end of treatment will be analysed for changes in MM cell biology and metabolism. These include examining clonal evolution and gene expression in MM cells, shifts in immune cell profile in marrow, and levels of metabolic hormones. Serum and plasma will be used for exploratory metabolomic and proteomic analyses to generate hypotheses on the biological impact of TRE. The microbiome has been linked to cancer pathologies and treatment [22]. It largely contributes to immune system maturation [31] and diet is a main driver of both microbiome composition and function [29]. Thus, TRE-induced microbiome changes could contribute to treatment outcome. Microbiome composition will be monitored using metagenomic sequencing.

## Sample size

The sample size for this trial was based on precision for the adherence endpoint, not statistical power for efficacy. We set a target that ≥ 80% of patients in the TRE arm must achieve adequate adherence for the intervention to be deemed feasible. Using a one-sample proportion calculation, enrolling 27 patients in the experimental arm allows the adherence rate to be estimated with a margin of error of approximately ± 15% at 95% CI. Therefore, 54 patients were chosen to assess feasibility with adequate precision. This sample also matches typical pilot trial sizes in oncology and is sufficient to identify major safety or compliance issues.

## Randomisation and blinding

Eligible patients are randomised immediately after screening using permuted blocks to ensure unpredictability. Allocation concealment is maintained via a secure web-based randomisation module in the electronic data capture system.

The trial is not blinded. Participants know their group assignment as they must actively follow or not follow a fasting schedule, and study clinicians also know which arm a patient is in. Treating physicians are instructed to manage patients uniformly according to clinical guidelines and not alter therapy based on arm assignment. Outcome assessors for survival and disease progression are inherently unblinded since they are involved in patient care, but progression is determined by IMWG criteria to maintain consistency.

An independent DMC is instituted to provide oversight of safety and trial conduct. The DMC is unblinded and will review interim safety data. They will monitor AE rates in both arms, focusing on harm signals in the TRE group. The DMC is empowered to recommend protocol modifications or early trial termination if unacceptable risks or futility are observed.

## Statistical methods

All analyses will follow the ITT principle. A per-protocol (PP) analysis will be performed as a sensitivity analysis. Safety analyses will include all patients who started the intervention or control and may be stratified by actual fasting behaviour if crossovers occur.

For the primary endpoint feasibility, the adherence rate in arm A will be calculated as patients with ≥ 80% fasting-day compliance divided by total patients in arm A, with a 95% CI (Clopper-Pearson). No hypothesis test is needed for this single-arm feasibility measure, and we will compare the observed adherence to our target threshold.

For the preliminary efficacy endpoint of CR with MRD negativity at T_1_, proportions between both arms will be compared using a chi-square or Fisher’s exact test to explore differences. We will estimate the absolute difference in CR/MRD rates between arm A and B with CI. To adjust for potential imbalances and our stratification factors, we will perform logistic regression: The dependent variable will be CR/MRD-negative status, and independent variables will include treatment arm, line of therapy, baseline BMI category, and gender. The logistic regression will provide an adjusted OR with a 95% CI for achieving CR/MRD negativity, yielding a hypothesis-generating effect size. We will examine MRD negativity alone and CR (regardless of MRD) separately as post hoc analyses.

Secondary endpoint analysis will be descriptive and exploratory: Response categories (VGPR, PR, SD) will be tabulated by arm. Survival endpoints (PFS, OS) will be plotted using Kaplan–Meier curves. Continuous measures like weight, BMI, and lab values will be analysed using mixed-effects models or paired t-tests within arms and compared between arms by analysis of covariance (ANCOVA), adjusting for baseline. AEs will be summarised by category and grade. QoL and fatigue scores will be analysed by calculating changes from baseline to T_1_. Mean changes will be compared between arms using t-tests or non-parametric tests if data are not normally distributed. Exploratory biological endpoints will be analysed for hypothesis-generation.

We anticipate minimal missing data for primary endpoints since adherence can be assessed if diary data are > 80% complete. Participants who discontinue TRE or withdraw before adherence can be evaluated will be counted as non-adherent for the feasibility endpoint, and intervention pauses and reasons will be summarised descriptively. If a patient lacks MRD status at T_1_, they will be considered not achieving CR/MRD. Missing data in secondary patient-reported outcomes will be handled by analysing available cases or using imputation methods. For survival, standard censoring at last follow-up is done for those without events. A sensitivity analysis using multiple imputation for missing outcome data will be explored to ensure robustness.

All statistical tests will be two-sided, with *p*-value < 0.05 considered significant for exploratory, hypothesis-generating purposes. No adjustments for multiple comparisons are planned, given the exploratory nature.

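### The response outcome is defined as either CR or MRD negativity but analysed as both together, and the missing-MRD rule fits only the second definition

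*Protocol article*

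**What the plan says.** All references are to the protocol article.

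- Primary outcomes lists therapy response as the second of two primary outcomes: "The combined rate of CR and/or MRD negativity in bone marrow (BM) at end of therapy". Either component is enough. The same entry limits its role: "The fraction will be compared between arms as an exploratory efficacy signal".
- Statistical methods introduces the analysis at T1 with "For the preliminary efficacy endpoint of CR with MRD negativity", which requires both components. It then moves to a shorthand. The risk difference is for CR/MRD rates, and for the regression "The dependent variable will be CR/MRD-negative status". The slash is not explained.
- The same section adds: "We will examine MRD negativity alone and CR (regardless of MRD) separately as post hoc analyses".
- On missing data it states: "If a patient lacks MRD status at T_1_, they will be considered not achieving CR/MRD". No exception is made for a patient whose CR is documented. Multiple imputation for missing outcomes is mentioned as a sensitivity analysis to be explored.

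**The concern.** The two sections define different sets of responders, a union and an intersection. A statistician working from Primary outcomes and one working from Statistical methods would code a patient with CR and residual disease, or with MRD negativity short of CR, in opposite ways. The test, the risk difference and the odds ratio would all follow that choice.

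The missing-MRD rule depends on the same choice. Under the union, a patient with documented CR has met the endpoint whatever the marrow MRD result, so calling that patient a failure contradicts the definition. Under the intersection, the second component is unknown and the rule is ordinary conservative non-responder imputation.

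The Discussion says that the CR/MRD endpoints are there to provide effect sizes and variability for a future trial, and it names a preliminary response signal as part of the case for phase II. A rate whose definition is open cannot be used as a planning value. In an open-label trial, the definition should also not be chosen after results are visible.

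**Working it through.** **The plan's own figure.** The article calculates nothing for the response outcome. Its one calculated figure is the adherence margin in Sample size, and it reproduces: 1.96 × √(0.80 × 0.20 / 27) = 0.151, against the stated ±15%. No response rate enters it, so the 54 patients (27 per arm) are unaffected.

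**How each patient type is coded.**

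| CR at T1 | MRD at T1 | Union (Primary outcomes) | Intersection (Statistical methods) | Missing-MRD rule |
|---|---|---|---|---|
| yes | negative | response | response | not used |
| yes | positive | response | failure | not used |
| yes | missing | response | unknown | failure |
| no | negative | response | failure | not used |
| no | positive | failure | failure | not used |
| no | missing | unknown | failure | failure |

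The definitions disagree in rows two and four. In row three the rule contradicts the union but only imputes under the intersection. In row six it imputes under the union and changes nothing under the intersection. So the rule is compatible with the intersection throughout and in conflict with the union in one row.

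**Size of the gap between definitions.** The article gives no CR rate, MRD-negative rate or overlap. Assume CR 30% and MRD-negative 30%, and vary the overlap. Union = 0.30 + 0.30 − overlap; intersection = overlap.

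| Overlap (assumed) | Union | Of 27 | Intersection | Of 27 | Gap |
|---|---|---|---|---|---|
| 10% | 50% | 13.5 | 10% | 2.7 | 40 points |
| 20% | 40% | 10.8 | 20% | 5.4 | 20 points |
| 30% | 30% | 8.1 | 30% | 8.1 | 0 points |

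The gap vanishes only if CR and MRD negativity coincide in every patient.

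**Size of the missing-MRD effect, if the union governs.** Take the 20% overlap (true union rate 40%) and let a fraction m of patients lack MRD, independently of response (assumption).

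- Rate under the stated rule: 0.40 × (1 − m).
- Rate if documented CR counts regardless: 0.30 + (0.30 − 0.20) × (1 − m).
- Documented CRs scored as failures per arm: 0.30 × m × 27.

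| m (assumed) | Stated rule | Documented CR counted | CRs misclassified per arm |
|---|---|---|---|
| 5% | 38.0% | 39.5% | 0.4 |
| 10% | 36.0% | 39.0% | 0.8 |
| 20% | 32.0% | 38.0% | 1.6 |
| 30% | 28.0% | 37.0% | 2.4 |

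**Unequal missingness, if the union governs.** With no true difference and MRD missing in 10% of one arm and 20% of the other, the stated rule creates a difference of 0.40 × (0.20 − 0.10) = 4 points. Counting documented CR leaves (0.30 − 0.20) × (0.20 − 0.10) = 1 point.

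**The case against.** The best defence is that Statistical methods is consistent with itself. It names the intersection, its missing-data rule fits the intersection, and the wording in Primary outcomes may simply be loose. On that reading there is one defect, and the missing-MRD rule is sound. This stands as a limit on the point. A reader might infer that the plan turns complete responders into failures. The documents support that only if the Primary outcomes definition governs, and they do not say that it does.

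A reader might also infer a twofold gap between the definitions, or a biased treatment comparison. The twofold figure belongs to one assumed overlap; at the same marginal rates the gap runs from 0 to 40 points over the overlaps shown. Missing MRD above 10% would exceed what the plan's own progression criterion of at least 90% completeness allows, if MRD counts as key clinical data; at 10% the loss is 0.8 patients per arm. Nothing in the article suggests that samples will be missed more often in one arm. Clinicians are told to treat both arms alike, and MRD is read blinded. Blinded reading does not govern whether a sample is taken, so unequal missingness is possible but not shown. A 4-point artefact is also small beside the sampling error: at an assumed 40% rate, the 95% half-width for the difference is 1.96 × √(2 × 0.40 × 0.60 / 27) = 0.26, about 26 points.

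Finally, the comparison is declared exploratory, none of the six progression criteria uses response, and CR and MRD negativity will also be reported separately. These points limit the harm. None of them says which patients are responders in the main analysis.

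**Conclusion.** The contradiction is real, lies in the current text and is not resolved elsewhere in the article: one of the two listed primary outcomes has two incompatible definitions. The missing-MRD point is conditional. It is a misclassification under the union and acceptable conservative imputation under the intersection.

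The size cannot be derived from the article. At assumed rates of 30% for each component, the definitions differ by 0 to 40 points for overlaps of 30% down to 10%. Under the union, 5 to 30% missing MRD misclassifies about 0.4 to 2.4 documented CRs per arm of 27. The sample size and the progression criteria do not depend on this. The effect-size estimate intended for the next trial does. Calling the separate CR and MRD analyses post hoc, although they are specified in advance, is a minor labelling error that changes no number.

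**What to change.** State one definition in Primary outcomes and in Statistical methods, including its missing-data paragraph, before outcome data are analysed. Use it for the test, the risk difference and the logistic regression, and replace the bare CR/MRD label. The documents do not show which definition was intended, so the sponsor must choose.

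- **If either component suffices:** count documented CR or documented MRD negativity at T1 as a response, whatever the availability of the other component. Apply the failure rule only when neither is documented.
- **If both are required:** correct Primary outcomes. The missing-MRD rule can then stand as conservative imputation.

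In both cases keep multiple imputation as the sensitivity analysis. Report the definition not chosen, CR alone and MRD negativity alone as pre-specified supportive analyses, and drop the post hoc label. The cost is protocol and analysis-plan wording only, with no new data and no change to the sample size.

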## Methods

### Trial design

FASTINA is an open-label, parallel-group, single-centre randomised feasibility trial evaluating TRE during standard MM therapy. 54 patients at the University Hospital Schleswig–Holstein (UKSH) – Campus Lübeck, will be randomised 1:1 to two arms: Arm A (experimental): 16:8 TRE (daily 16 h fasting/8 h eating window) for 12 weeks in addition to standard nutritional counselling. Arm B (control): Standard nutritional counselling alone for 12 weeks (no fasting intervention). The 16:8 schedule was selected as a pragmatic compromise between a fasting interval long enough to induce daily metabolic switching and an 8 h eating window that still permits patients to meet energy and protein goals during therapy. More restrictive prolonged fasting was avoided for safety reasons.

All participants continue their standard-of-care anti-MM therapy per guidelines. Trial duration is ≈ 7 months, including 28 d screening, a 12-week intervention during active MM therapy, and 12-week follow-up. Key time points are baseline (T_0_), end of the 12-week intervention (T_1_), and end of the 12-week follow-up (T_2_) (Fig. 2).

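### QLQ-C30 is collected at the end of follow-up (T2), but the stated quality-of-life analysis is an unadjusted comparison of change to T1, so the T2 scores have no stated analysis

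*Protocol article*

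**What the plan says.** The Quality of life (QoL) section of the protocol article gives three assessment times: "Patient-reported outcomes will be measured using the EORTC QLQ-C30 questionnaire at baseline, end of treatment, and end of follow-up". Under Trial design these are T0, T1 and T2, with "a 12-week intervention during active MM therapy, and 12-week follow-up". The Fatigue section names the instrument, "Fatigue will be assessed by the FACIT-fatigue scale", and lists no visits.

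Statistical methods places all secondary outcomes under one description: "Secondary endpoint analysis will be descriptive and exploratory". It then treats two groups of continuous outcomes differently.

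- Weight, BMI and laboratory values: "Continuous measures like weight, BMI, and lab values will be analysed using mixed-effects models or paired t-tests within arms", with arms compared by ANCOVA adjusting for baseline.
- Quality of life and fatigue: "QoL and fatigue scores will be analysed by calculating changes from baseline to" T1, followed by "Mean changes will be compared between arms using t-tests or non-parametric tests if data are not normally distributed".

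The same section allows missing patient-reported data to be handled by available cases or by imputation, and plans no multiplicity adjustment. It states no analysis of quality of life at T2, whether descriptive or comparative.

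**The concern.** The article is not silent on how quality of life will be analysed. It names a time point (T1) and a method (a two-sample test on change scores). Read against the assessment schedule, that leaves the T2 questionnaire without a stated use in the analysis. T2 is the only scheduled QLQ-C30 assessment that falls after the intervention period, so it alone could show whether a between-arm difference is maintained, fades or reverses once the 12 weeks are over.

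Two things are at stake. First, if a T2 comparison is added later, nothing in the published text shows that it was planned. Second, the Discussion wants a future trial to use robust patient-reported measures, and an estimate with its variability at both visits would help design it. The unadjusted change-score test is also a weaker choice than the baseline-adjusted methods that the same section already applies to other continuous outcomes.

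**Working it through.** **Schedule against analysis**

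- QLQ-C30 collected: baseline, T1, T2 (Quality of life section).
- QLQ-C30 analysed: change from baseline to T1, compared between arms (Statistical methods).
- Collected without a stated analysis: T2.
- Could another sentence cover T2? The mixed-model and ANCOVA sentence gives weight, BMI and laboratory values as its examples, and quality of life and fatigue have their own sentence. The missing-data paragraph names no visit for patient-reported outcomes. Progression criterion IV concerns completeness of data, not comparison. None supplies a T2 analysis.

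**The plan's own precision figure**

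The only one is the margin of about ±15% for adherence with 27 patients in arm A. At 80% adherence, 1.96 × √(0.80 × 0.20 / 27) = 0.151, so it reproduces. It concerns adherence only and has no bearing on this point.

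**What a T2 contrast could deliver**

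For a difference in mean change between two arms of n patients each, the 95% CI half-width in units of the SD of the change is t(0.975; 2n − 2) × √(2/n).

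- n = 27 (54 randomised 1:1, full retention): 2.007 × √(2/27) = 2.007 × 0.2722 = 0.55 SD.
- n = 23 (27 × 0.85 = 22.95, assuming that the 85% retention criterion, which the article sets only to the primary endpoint, carries to T2): 2.015 × √(2/23) = 2.015 × 0.2949 = 0.59 SD.
- n = 20 (assumed): 2.024 × √(2/20) = 2.024 × 0.3162 = 0.64 SD.

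The article gives no T2 retention figure, so the two lower numbers are illustrations.

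**Baseline adjustment**

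Take an equal SD σ at baseline and follow-up and a correlation ρ between them. The change score has variance 2σ²(1 − ρ), and the baseline-adjusted residual has variance σ²(1 − ρ²). Their ratio, adjusted to change score, is (1 + ρ)/2, which never exceeds 1. Apart from the degree of freedom spent on baseline, the adjusted interval is therefore no wider than those above, and it is narrower whenever ρ is below 1.

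**The case against.** The strongest reply is that nothing here contradicts anything. Measuring at three visits and choosing the end of the intervention as the compared time point is coherent. The text does not say that only T1 will be reported, no objective about persistence is stated, and a condensed article may leave T2 to the full protocol or analysis plan. This stands in part: the consequence is limited to the absence of a *stated* T2 analysis. It does not remove the point, because the article chooses a time point and a test explicitly, and a better method is available for data already being collected.

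A reader might infer more than the documents support:

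- *The trial will be unable to say anything about persistence.* An unseen plan could include a T2 analysis.
- *Half of the post-baseline questionnaires serve no purpose.* Progression criterion IV asks for at least 90% completeness of key patient-reported data without naming a visit, so T2 forms may count towards it.
- *Fatigue may not be measured at T2.* The Fatigue section lists no visits, but the trial schema is not shown. Its legend defines FACIT and places assessments at T1 and T2.
- *A patient without a T1 form is lost.* The missing-data paragraph allows imputation.
- *T1 is the visit most coloured by expectation.* The article acknowledges open-label bias in self-reported outcomes but does not say that it differs by visit, and patients remain unblinded at both.

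Imprecision is also a fair objection. At these numbers a T2 interval excludes zero only if the observed difference is more than about half an SD. That is a reason to label the estimate exploratory, not to leave it unstated.

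**Conclusion.** The point holds as a minor one. The QLQ-C30 is collected at T2, the stated analysis is an unadjusted between-arm comparison of change to T1, and the T2 scores have no stated analysis. The stated quality-of-life analysis therefore does not address persistence after the intervention. No primary outcome, sample-size figure or progression criterion is affected.

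The conclusion rests on the article alone and would lapse if the analysis plan already specifies a T2 estimate. Any T2 estimate would have a 95% CI half-width of roughly 0.55 SD at full retention and 0.59 to 0.64 SD under the assumed losses. It would compare the arms as randomised: MM therapy or eating habits may change between T1 and T2, so it should not be read as a pure carry-over effect of TRE.

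**What to change.** In Statistical methods, replace the t-test on change scores with one mixed model for repeated measures, with arm, visit, arm-by-visit interaction and baseline score as terms. Report the between-arm difference with its 95% CI at T1, named as the main time point, and at T2, named as an exploratory estimate of persistence. Apply the model to quality of life, and to fatigue wherever it is collected at T2.

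The cost is a change of wording and one more exploratory, imprecise estimate per scale. Sample size and alpha are unaffected, because these analyses are exploratory and unadjusted for multiplicity, and no new quality-of-life visit or questionnaire is required. Mixed models and baseline adjustment are already planned for other continuous outcomes. With 8 patients randomised at submission, the change can still be made early in the trial.

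### Quality of life and fatigue are compared by unadjusted tests on change scores, while the same paragraph plans baseline-adjusted ANCOVA for the other continuous outcomes; extending the ANCOVA would cost nothing and usually gain precision.

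*Protocol article*

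**What the plan says.** All references are to the protocol article.

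- **Patient-reported outcomes (Statistical methods).** The outcome variable is a change score: "QoL and fatigue scores will be analysed by calculating changes from baseline to T_1". The between-arm comparison follows: "Mean changes will be compared between arms using t-tests or non-parametric tests if data are not normally distributed". No covariate is named, and the only ground for leaving the t-test is non-normality.
- **Other continuous measures (same paragraph).** Weight, BMI and laboratory values are "compared between arms by analysis of covariance (ANCOVA), adjusting for baseline". No reason is given for handling the two groups of outcomes differently.
- **Baseline data.** The section on quality of life schedules the "EORTC QLQ-C30 questionnaire at baseline, end of treatment, and end of follow-up". The section on fatigue names the instrument ("Fatigue will be assessed by the FACIT-fatigue scale") without time points, but a change from baseline cannot be computed without a baseline score, so one is implied.
- **Size and status.** Under Trial design, 54 patients "will be randomised 1:1 to two arms", which gives 27 per arm. The secondary analyses are labelled descriptive and exploratory, and two-sided tests at 0.05 are to be read in that spirit.

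**The concern.** A change score subtracts the whole baseline value, as if the regression of the T1 score on baseline had slope 1. With equal SDs the slope equals the correlation, which is below 1, so subtraction over-corrects: an arm that happens to start higher will tend to show a smaller gain. ANCOVA estimates the slope from the data and removes this dependence.

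Two things are at stake for these outcomes. The first is precision in a trial with at most 27 patients per arm. The second is that the reported difference can partly reflect where the arms started. Stratification covers line of therapy, BMI category and gender, but neither baseline quality of life nor baseline fatigue. The non-parametric fallback has the same weakness, because it too is applied to unadjusted changes.

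**Working it through.** **1. The plan's own figure.** The only precision statement concerns adherence: "enrolling 27 patients in the experimental arm allows the adherence rate to be estimated with a margin of error of approximately ± 15% at 95% CI". With the 80% target from the Sample size section, the Wald half-width is 1.96 × √(0.8 × 0.2 / 27) = 0.151, so the stated figure reproduces. No precision is stated for quality of life or fatigue; what carries over is n = 27 per arm.

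**2. Inputs.** From the documents: 27 per arm, baseline and T1 scores, change-score test. Assumed, because the documents do not give them: the baseline-T1 correlation ρ, shown from 0.3 to 0.8, and equal SDs at baseline and T1 (relaxed in step 5).

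**3. Precision.** In units of the common variance s², per patient:

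- Var(change) = 2s²(1 − ρ)
- Var(ANCOVA) = s²(1 − ρ²)
- Ratio = (1 + ρ)/2; standard-error reduction = 1 − √ratio
- 95% CI half-width = 1.96 × √(variance × 2/27)

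| ρ | Variance ratio | SE reduction | CI half-width, change score (SD) | CI half-width, ANCOVA (SD) | Patients a change score needs to match ANCOVA with 54 (54/ratio) |
|---|---|---|---|---|---|
| 0.3 | 0.65 | 19.4% | 0.63 | 0.51 | 83 |
| 0.5 | 0.75 | 13.4% | 0.53 | 0.46 | 72 |
| 0.7 | 0.85 | 7.8% | 0.41 | 0.38 | 64 |
| 0.8 | 0.90 | 5.1% | 0.34 | 0.32 | 60 |

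These formulas ignore the small cost of estimating the slope. A simulation of 40,000 trials with 27 per arm includes it and gives ratios of 0.66, 0.77 and 0.86 at ρ = 0.3, 0.5 and 0.7.

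**4. Chance baseline imbalance.** The baseline difference between arms has standard error √(2/27) = 0.27 SD. The probability that it exceeds 0.25 SD in either direction is 36%; for 0.5 SD it is 6.6%. Given a realised difference d, the change-score estimate shifts by −(1 − ρ)d. For d = 0.25 SD:

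- ρ = 0.3: 0.7 × 0.25 = 0.175 SD
- ρ = 0.5: 0.5 × 0.25 = 0.125 SD
- ρ = 0.7: 0.3 × 0.25 = 0.075 SD
- ρ = 0.8: 0.2 × 0.25 = 0.05 SD

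In the simulation the change-score estimate correlated −0.59, −0.50 and −0.39 with the baseline difference at ρ = 0.3, 0.5 and 0.7; the ANCOVA estimate correlated about 0. Averaged over all simulated trials, both estimates were centred on the true difference of zero.

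**5. Unequal SDs.** With SD s₀ at baseline and s₁ at T1, Var(change) = s₀² + s₁² − 2ρs₀s₁ and Var(ANCOVA) = s₁²(1 − ρ²). For ρ = 0.7 and s₁/s₀ = 1.3 (assumed), with s₀ = 1:

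- Var(change) = 1 + 1.69 − 1.82 = 0.870
- Var(ANCOVA) = 1.69 × 0.51 = 0.862

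The gain almost disappears. In general the difference of the two variances is (s₀ − ρs₁)². It is never negative, but it is zero where ρs₁ = s₀.

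**The case against.** The strongest reply is that nothing here is invalid. Under randomisation the t-test on change scores is unbiased on average and keeps its type I error, the outcomes are secondary and exploratory, and the trial is sized on adherence. All of that stands, and it limits the point to precision, conditional imbalance and consistency. It is also true that the size of the gain depends on a correlation and an SD ratio that the documents do not give, and that the gain can be negligible.

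Leaving the detail to an unseen analysis plan is not a full answer. The article does not omit the method; it names one, and it is the weaker of two methods used in the same paragraph. Nor can these scores be read into the ANCOVA sentence, because they have a sentence of their own.

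A reader might infer more than the documents support:

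- **That these estimates will size the next trial.** The Discussion gives that role to the CR/MRD endpoints and foresees response rate or PFS as the next primary endpoint. The Progression criteria use the completeness of patient-reported data, not an arm difference.
- **That the within-arm paired t-tests replace a between-arm comparison.** The same sentence supplies that comparison by ANCOVA.
- **That T2 scores and the stratification factors are excluded from the continuous analyses.** The article does not say so. QLQ-C30 is collected "at baseline, end of treatment, and end of follow-up", the T1 contrast matches the end of the intervention, and full covariate lists and the handling of T2 can be left to a fuller document.

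**Conclusion.** The point holds as a modest, optional improvement. The article fixes an unadjusted change-score comparison for QLQ-C30 and FACIT-fatigue, although baseline scores are available (for fatigue by implication) and ANCOVA is already planned next to it. With equal SDs and a correlation of 0.3 to 0.8, both assumptions, ANCOVA lowers the standard error by about 19% to 5%. The gain is smaller if the T1 SD is moderately larger than the baseline SD, and close to nil at a correlation of 0.7 with an SD ratio of 1.3. A chance baseline difference of 0.25 SD, which is not unusual at this size, moves the change-score estimate by 0.125 SD at a correlation of 0.5. Adherence, the progression criteria and the feasibility conclusion are unaffected.

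**What to change.** In Statistical methods, replace the change-score comparison for QLQ-C30 and FACIT-fatigue with the ANCOVA already planned for weight, BMI and laboratory values: T1 score as outcome, arm and baseline score as covariates, preferably with line of therapy, BMI category and gender added. Report the adjusted mean difference with its 95% CI. If the data are clearly non-normal, use a bootstrap interval or a rank-based ANCOVA, so that the baseline adjustment is kept. State in the Fatigue section that FACIT-fatigue is collected at baseline and T1.

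The cost is a change of wording. No visit, questionnaire or sample is added beyond what the change-score analysis already needs. With 8 patients randomised at submission, the change can be made well before outcomes are analysed.
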